### Procedures

Prior to orientation, welcome letters containing the schedule of group sessions and directions are mailed. Reminder calls are placed to facilitate continued interest in the study. Participants attend orientation, eight clinic sessions, and 3, 6, and 12-month follow-up assessments.

### Interventions

#### Orientation and intervention sessions

Participants attend a 60-minute orientation before the start of the clinic sessions. They learn the background, purpose, format, and procedures of the study; provide informed consent; complete baseline measures; learn about TNP therapy and receive their first patch (the remainder of the patches are provided throughout active treatment); and provide breath carbon monoxide (CO) and saliva samples for cotinine analysis. We also cover smoking and health, self-motivation, and goal setting. In the CS-CBT condition, we explain that the group is framed within a cultural context, designed to emphasize African American race/ethnicity and cultural issues.

In accordance with previous research (Webb et al. 2010;Brandon et al. 1995) participants in both conditions are asked to reduce their smoking by one-half on the day before the first clinic session and to abstain completely from smoking on the first day of actual group treatment (session 1). They are also instructed to begin patch use on the morning of the first day of treatment (session 1; the target quit day) with the patch provided at orientation. This aspect of the protocol is unique from other cessation approaches that set the quit day several weeks post beginning the intervention. However, this evidence-based protocol has been successful in previous studies [e.g., Webb et al. 2010; Brandon et al. 1995 and is also the format we use in our ongoing cessation clinic. Participants who do not quit on the target day are encouraged to make a quit attempt by the third treatment session.

Participants in both conditions meet eight times over four consecutive weeks. Four sessions occur during week 1, two during week 2, and one weekly booster session during weeks 3 and 4. Depending on group size, the duration of sessions is 90–120 minutes in both conditions. We anticipate 8–16 participants per group. Co-therapy pairs of masters or bachelor’s level interventionists are trained to conduct sessions for one condition (CS-CBT or control) and supervised by the principal investigator (PI). Groups are held in a laboratory-based clinic. Incentives include $40 at session 1, $20 at session 5, $50 at session 8, $50 at the 3-month assessment, $70 at the 6-month assessment, and $70 at the 12-month assessment. Participants also receive $5 per session for transportation/parking and light refreshments at each session.

#### Intervention conditions

*Group cognitive behavioral therapy for smoking cessation (control):* The intervention in this condition is based on standard cognitive and behavioral strategies, supplemented by TNP therapy. A previous study testing this intervention in an African American sample found 7-day ppa rates of 70% at the EOC, 52% at the 3-month follow-up, and 46% at the 6-month follow-up post counseling (Webb et al. 2010). Session content is displayed in Table 1, and includes the benefits of quitting, nature of nicotine addiction, nicotine withdrawal, identification of “high risk” situations, motivation, coping skills, stress and negative affect, decision making, alcohol use, weight control, social support, behavioral contracting, and relapse-prevention. To enhance the external validity of the intervention, the co-therapy team is not race-matched (at least one interventionist is non-African American/Black).*Culturally specific group cognitive behavioral therapy for smoking cessation (CS-CBT):* The intervention is the standard CBT program with an emphasis on African American culture (Table 1). Each session focuses on specific aspects of traditional African American culture. The CS topics were selected based on our previous qualitative research (Webb et al. 2007), and established models e.g. (Robinson et al. 1992). Topics include deep structure: Distrust for biomedical research; race and smoking, race-based statistics related to nicotine replacement/medication concerns; religion/spirituality; family/collectivism; unique stressors; racism/discrimination, depression among African Americans; co-morbid addiction; neighborhood/environmental influences; targeted tobacco marketing; menthol cigarettes; race-specific weight issues and concerns; and working as a community against the tobacco industry. Surface structure is also included: Interventionists are race-matched, second-person phrases (e.g., us, we) are used throughout, and the daily agenda includes African American quotations or proverbs.

**Table 1 Tab1:** **Overview of the interventions**

	CBT	CS-CBT
**Orientation**	Study explanation, structure of sessions and TNP, informed consent, health and smoking, research participation, goal setting, baseline assessment, breath carbon monoxide (CO) and saliva samples.	Same as in the CBT condition. Race and smoking, views on research participation, distrust for biomedical research, concerns about nicotine replacement, goal setting, baseline assessment, breath CO and saliva samples, race-matched clinicians (RMC).
**Session 1**	Review quit plan, positive reinforcement (PR), reasons for quitting, nicotine addiction, introduction to coping response training model, smoking and motivation, TNP use, plan for next 24 hours, behavioral contracting (BC), CO.	Standard CBT. Meaning of being African American, tobacco and African Americans, menthol, RMC.
**Session 2**	Review quit plan progress, PR, benefits of quitting, coping skills, plan for next 24 hours, BC, CO.	Standard CBT. Spirituality and religion in the African American community, RMC.
**Session 3**	Review quit plan progress, PR, stress management, alcohol and smoking, high cost of smoking, plan for next 48 hours, perceived benefits of quitting, BC, CO.	Standard CBT. Stressors unique to African Americans, discrimination and racism, deep breathing exercises, co-morbid addiction, little cigars and blunt use, RMC.
**Session 4**	Review quit plan progress, PR, negative affect and smoking, cognitive restructuring, decision making, plan for next 72 hours, BC, CO.	Standard CBT. Traditional African American values, buddy system, deep breathing exercise, RMC.
**Session 5**	Review quit plan progress, PR, review personal high-risk situations, relapse prevention, responding to lapses, plan for next 72 hours, BC, CO.	Standard CBT. Mood and depression among African Americans, deep breathing exercise, RMC.
**Session 6**	Review quit plan progress, PR, individual high-risk situations, noted benefits of quitting, weight and smoking cessation, minimizing weight gain, relapse prevention, plan for next 7 days, BC, CO.	Standard CBT. Weight and African Americans, smoking and weight concerns (super-gainers), minimizing weight gain (physical activity with limited resources, healthy food choices within soul food diet, recipes), deep breathing, RMC.
**Session 7**	Review quit plan progress, PR, planning for group termination, a new lifestyle, social support, plan for next 7 days, BC, CO.	Standard CBT. Life in your neighborhood, environmental influences, gaining freedom from smoking, deep breathing exercise, RMC.
**Session 8**	Review quit plan progress, PR, reflect on group experience, long-term trip-ups, review of coping response training, withdrawal, relapse prevention, TNP schedule, follow-up procedures, BC, CO and saliva samples.	Standard CBT. Body as a temple, resources, mobilizing the African American community against the tobacco industry, deep breathing exercise, RMC.

Note: Topics that are not explicitly culturally specific are discussed within this context.

#### Transdermal nicotine patch therapy (TNP)

TNP has demonstrated efficacy in multiple trials (Silagy et al. 2000), is available over-the-counter, and is safe and effective for smoking cessation (Shiffman et al. 2002) without monitoring by a physician. Consistent with (Webb et al. 2010) and (Fiore et al. 2008), participants are prescribed four weeks at 21 mg, two weeks at 14 mg, and two weeks at 7 mg (Doses are adjusted according to smoking history).

#### Training and intervention fidelity

The interventionists are trained by the PI. Training includes relevant readings (smoking, cessation and relapse prevention, cognitive behavioral therapy, motivational interviewing), observation of two therapy groups, minimal contributions in the role of therapist, and finally, fully conducting sessions with weekly PI supervision. Detailed intervention manuals are followed closely and participants receive a daily agenda. Interventionists do not cross over to prevent contamination. Most sessions are audio recorded and will be coded using a 10-item scale for adherence [see Webb et al. 2010 by two independent evaluators. Codes will be transformed into percentages indicating the degree of protocol adherence.

### Measures

#### Baseline

Measures include demographics, smoking history, and nicotine dependence (Heatherton et al. 1991) (Table 2). We also assess perceived stress (Cohen et al. 1983), depressive symptoms (Radloff 1997), and decision making. Particularly relevant for African American smokers, we include assessments of acculturation (Klonoff & Landrine 1999), ethnic identity (Davis et al. 2010), expectancies for culturally specific interventions, and perceived ethnic discrimination (Landrine et al. 2006). We also record height and weight. Participants also complete an “In Case I Move Form” as a method of tracking participants via relatives or friends.

**Table 2 Tab2:** **Constructs and measures**

Assessment points						
Measure	Baseline	Intra-treatment	End-of-counseling	3-month follow-up	6-month follow-up	12-month follow-up
Attendance	✓	✓	✓	✓	✓	✓
Demographics	✓					
Smoking history	✓					
Nicotine dependence	✓					
Height	✓					
Weight	✓	✓	✓	✓	✓	✓
Perceived stress	✓		✓			
Depressive symptoms	✓		✓			
Acculturation	✓					
Ethnic Identity	✓					
Expectancies for culturally specific Interventions	✓					
Decision making	✓					
Perceived ethnic discrimination	✓					
Nicotine withdrawal		✓	✓			
Smoking urges		✓	✓			
TNP use		✓	✓			
Intervention ratings			✓			
Time-line follow-back (smoking pattern)			✓	✓	✓	✓
Therapist satisfaction			✓			
Carbon monoxide	✓	✓	✓	✓	✓	✓
Cotinine*	✓			✓	✓	✓

Note: *At baseline, saliva for cotinine is collected from all participants. Cotinine samples are not collected at the EOC because participants are still using nicotine replacement. At follow-ups, saliva for cotinine is collected from self-reported abstainers only.

#### Intra-treatment

Attendance, TNP utilization, and weight are recorded at each session. Participants also self-report, via monthly telephone follow-ups, utilization of 14mg, and 7mg patches across the full 8-weeks. The Minnesota Withdrawal Scale (Hughes & Hatsukami 1986) is administered as an indicator of nicotine withdrawal, and the Questionnaire of Smoking Urges-Brief (Sanderson Cox et al. 2001) assesses urges to smoke.

#### End-of-counseling

Participants evaluate the intervention, using the Intervention Rating Questionnaire (Webb et al. 2010), and complete measures of perceived stress, depressive symptoms, nicotine withdrawal, and therapist satisfaction (Oei & Green 2008) (Table 2). Self-reported smoking status since the target quit date is assessed using the time-line follow-back (TLFB) procedure, which reconstructs the participant’s smoking pattern since the target quit date (Brown et al. 1998;Sobell & Sobell 1992).

#### Follow-up (3, 6, and 12-months)

Measures completed at each “reunion meeting” include the TLFB (Brown et al. 1998;Sobell & Sobell 1992), smoking status and use of other tobacco products and pharmacotherapy, and weight (Table 2).

#### Bio-verification

Smoking status is confirmed biochemically. Cotinine assays are collected at the orientation meeting (for a baseline level before cessation) and at the in-person 3, 6, and 12-month follow-ups (for self-reported quitters). Cotinine samples, using a cut point of 7 ng/ml, will determine smoking status (Abrams et al. 1987;Etter et al. 2000). The CBT protocol requires that breath carbon monoxide (CO) samples be collected at each session to provide participants with immediate feedback. Breath CO readings of at least 8 ppm will distinguish smokers from nonsmokers at the EOC, and have been found to be a sensitive method of determining smoking status (Benowitz et al. 2002). As recommended by (Benowitz et al. 2002), follow-up abstinence rates will be calculated separately for both self-report and biochemical findings.

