**Methods/Design:**

A 2-arm randomized controlled trial (RCT) will be conducted to assess the efficacy of a culturally specific group cognitive behavioral therapy (CBT), compared to standard group CBT among treatment-seeking smokers from the community. Participants in both conditions receive the transdermal nicotine patch (TNP) for 8-weeks. We intend to randomize at least 247 adult smokers who self-identify as African American into the trial. Enrolled participants are block randomized into one of two groups: Standard group CBT (control) or a culturally specific group CBT (CS-CBT). Groups are matched for time and attention, and consist of eight sessions. The primary outcome variable is 7-day point prevalence abstinence (7-day ppa). Smoking status is assessed at the end-of-counseling (EOC), and 3, 6, and 12-month follow-ups, with self-reported abstinence verified by saliva cotinine. We hypothesize that the CS-CBT condition will produce significantly greater smoking cessation rates compared to the control condition. We also expect that this effect will be moderated by acculturation and ethnic identity, such that the CS-CBT will show the greatest effect on cessation among participants who are less acculturated and have greater ethnic identity.

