#### Outcome variables

The primary outcome variable is 7-day ppa, assessed at the EOC, 3, 6, and 12-month follow-ups. Seven-day ppa refers to no smoking (not even a puff) for the past seven days (Hughes et al. 2003). Secondary outcomes include 24-hour (no smoking in the past day) and 28-day continuous abstinence (no smoking over the past 4 weeks).

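### At 3, 6 and 12 months the single cotinine rule outlasts the 24-hour window, so the biochemical version of the 24-hour secondary outcome scores some recent abstainers as smokers

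*Protocol article*

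**What the plan says.** The Bio-verification section opens with a general statement, "Smoking status is confirmed biochemically", and then gives the follow-up criterion: "Cotinine samples, using a cut point of 7 ng/ml, will determine smoking status". The Methods/Design part of the abstract lists the assessments and adds "with self-reported abstinence verified by saliva cotinine". Neither place limits the rule to a particular definition of abstinence.

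The Outcome variables section defines the primary outcome ("Seven-day ppa refers to no smoking (not even a puff) for the past seven days") and then the others: "Secondary outcomes include 24-hour (no smoking in the past day) and 28-day continuous abstinence (no smoking over the past 4 weeks". It gives no separate verification rule for any of them.

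Breath CO has a classifying role at one assessment only: "Breath CO readings of at least 8 ppm will distinguish smokers from nonsmokers at the EOC". Table 2 shows CO also being measured at 3, 6 and 12 months, but no section says what it decides there. The note to Table 2 adds "At follow-ups, saliva for cotinine is collected from self-reported abstainers only".

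Finally, the Bio-verification section says that "follow-up abstinence rates will be calculated separately for both self-report and biochemical findings".

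**The concern.** A marker used to verify abstinence over a given window should not stay positive well beyond that window. Cotinine is cleared slowly. A person who smoked two days before a follow-up visit satisfies the 24-hour definition, but may still be above 7 ng/ml and so be counted as a smoker once the biochemical rule is applied.

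At stake is the meaning of the biochemically verified 24-hour rate at 3, 6 and 12 months. It would run below the true 24-hour rate and towards a rate of abstinence over several days, closer to the 7-day outcome that it is meant to complement. At EOC the same outcome is classified by CO, so the biochemical standard changes between EOC and 3 months. If this outcome is modelled over time, as the Statistical analyses section plans for cessation rates, part of any fall after EOC could come from the change of marker.

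**Working it through.** The plan states no figure that can be reproduced here; 7 ng/ml is a fixed threshold. The question is how long a person stays above it after the last cigarette.

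**Inputs**
- Cut point: 7 ng/ml (Bio-verification).
- Outcome windows: 1, 7 and 28 days (Outcome variables).
- Cotinine half-life: not in the documents; assumed 12-24 h.
- Cotinine at the last cigarette (C0): not in the documents; assumed 50-500 ng/ml.
- No other source of nicotine after the last cigarette (assumed).

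**Formulas** (first-order decay)
- Time to the cut point = half-life × log2(C0 / 7).
- Level after t hours = C0 × 2^(−t / half-life).

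**Results**

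| C0 (ng/ml) | Half-life (h) | Level at 24 h (ng/ml) | Time to 7 ng/ml |
|---|---|---|---|
| 50 | 12 | 12.5 | 34 h (1.4 days) |
| 50 | 24 | 25 | 68 h (2.8 days) |
| 100 | 12 | 25 | 46 h (1.9 days) |
| 100 | 24 | 50 | 92 h (3.8 days) |
| 300 | 12 | 75 | 65 h (2.7 days) |
| 300 | 24 | 150 | 130 h (5.4 days) |
| 500 | 12 | 125 | 74 h (3.1 days) |
| 500 | 24 | 250 | 148 h (6.2 days) |

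For the shortest time, 12 × log2(50/7) = 12 × 2.84 = 34 h. For the longest, 24 × log2(500/7) = 24 × 6.16 = 148 h. In the middle of the range (half-life 16-20 h, C0 100-300 ng/ml) it is about 2.6 to 4.5 days.

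**At 24 hours.** Every scenario is still above 7 ng/ml. The highest starting level that clears within 24 h is 7 × 2^(24/half-life): 28 ng/ml at a 12 h half-life and 14 ng/ml at 24 h. Conversely, a person starting at 100 ng/ml would pass at 24 h only with a half-life of 24 / log2(100/7) = 6.3 h or less; from 50 ng/ml, 8.5 h or less.

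**At 7 days.** The worst case is 500 × 2^(−168/24) = 500/128 = 3.9 ng/ml, below the cut. The same threshold therefore fits the 7-day outcome and, all the more, the 28-day outcome. The mismatch is confined to the 24-hour outcome.

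**Who is affected.** Only participants whose last cigarette lies between 24 h and the clearance time, which is 1.4 to 6.2 days depending on the assumptions. The documents do not give the distribution of time since last cigarette among 24-hour abstainers, so their share cannot be computed.

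**The case against.** The strongest objection is that no section says in so many words that 24-hour abstinence is verified by cotinine. The Design and method section attaches cotinine confirmation to the primary outcome. Saliva is taken only from self-reported abstainers, and the window that makes someone an abstainer for this purpose is not stated. A condensed article may also leave the assignment of markers to a fuller document.

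Part of this stands: the link to the 24-hour outcome is inferred from a general rule. But the rule is stated without exception, so this is more than missing detail: followed as written, it covers an outcome that it does not fit. The open sampling window does not help. A person who smoked two days ago is either sampled and likely to fail, or not sampled and left without a biochemical status for this outcome.

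A second objection stands in full. A reader might infer that cotinine alone decides the 24-hour outcome at follow-up. It does not: a self-report rate is calculated separately and is untouched, although the article does not say which version is the 24-hour outcome.

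A reader might also infer that all true 24-hour abstainers are misscored, or that anyone within three days of a cigarette is far above the cut. Neither follows. Sustained quitters using no other nicotine pass. From 100 ng/ml with a half-life of 15-20 h, the level at 72 h is 3.6-8.2 ng/ml, at or around the threshold. An isolated slip could start lower and clear sooner.

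Lastly, the marker at each visit is the same in both arms, and the within-time regressions compare arms at the same visit. The switch from CO to cotinine therefore does not confound the randomized comparison at a visit.

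**Conclusion.** The point holds as a minor correction to one version of one secondary outcome. As written, the 7 ng/ml rule covers all biochemically verified abstinence at follow-up, and its detection window exceeds 24 hours under every combination of half-life (12-24 h) and starting level (50-500 ng/ml) tried. Both ranges are assumptions. The direction would reverse only for starting levels of about 14-28 ng/ml or less, or for half-lives well below the assumed range.

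The consequences are a downward bias in the biochemical 24-hour rate at 3, 6 and 12 months, of a size that the documents do not allow to be computed, and a comparison of EOC with 3 months that mixes two markers. It would go too far to conclude that the trial's main result is at risk: this mechanism does not touch the 7-day primary outcome, the 28-day outcome or the self-report 24-hour rate.

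**What to change.** In the Bio-verification section, limit the cotinine rule to the 7-day and 28-day outcomes. For 24-hour abstinence at 3, 6 and 12 months, choose one of two options and say so:

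- verify it with the breath CO that Table 2 already collects, under the same 8 ppm rule as at EOC, so that one standard applies at all four assessments; or
- designate it as self-report only at follow-up.

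The cost is a sentence of wording, with no new visit, sample or procedure. The CO option has two drawbacks. It can miss light smokers: the eligibility criteria admit people smoking at least 5 cigarettes a day whatever their CO, so an active smoker may read below 8 ppm. It can also be raised by smoke from sources other than tobacco. It further assumes that CO falls much faster than cotinine, for which the documents give no figure. The self-report option avoids these problems but leaves the outcome unverified at follow-up.

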#### Outcome variables

The primary outcome variable is 7-day ppa, assessed at the EOC, 3, 6, and 12-month follow-ups. Seven-day ppa refers to no smoking (not even a puff) for the past seven days (Hughes et al. 2003). Secondary outcomes include 24-hour (no smoking in the past day) and 28-day continuous abstinence (no smoking over the past 4 weeks).

### Data analyses

#### Sample size and power

Sample size was determined based on Webb et al. (2010) and the formula provided in (Diggle et al. 2002) (p. 31). Webb et al. 2010 found that 51% of participants who received standard CBT reported 7-day ppa at the EOC, and about a 20% relapse rate at 3-months and 6-months. In the CS-CBT pilot study, we found 75% 7-day ppa at the EOC. Assuming a 23% reduction at 3-months, four assessments, with a within-subjects correlation of .60, 65 participants per group will yield power = .80% with a two-sided significance level of 5%. We conservatively anticipated 30% 7-day ppa at 12-months in the CS-CBT condition, and 14% in the control condition. To examine acculturation and ethnic identity as moderators controlling for covariates (e.g., group, sociodemographic factors, etc.), the planned regression analyses require a sample of 124. Thus, the final N is 150 (completing all assessments).

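### The protocol gives the control arm's end-of-counseling abstinence as both 51% and 70%, from the same earlier trial and without denominators, so the 24-point difference behind the sample size cannot be verified.

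*Protocol article*

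**What the plan says.** Under Sample size and power, the control assumption is taken from one earlier trial of standard CBT: "51% of participants who received standard CBT reported 7-day ppa at the EOC, and about a 20% relapse rate at 3-months and 6-months". The comparison rate comes from the team's own pilot: "In the CS-CBT pilot study, we found 75% 7-day ppa at the EOC". The calculation then proceeds: "Assuming a 23% reduction at 3-months, four assessments, with a within-subjects correlation of .60", and concludes that "65 participants per group will yield power = .80" at a two-sided 5% level. A 12-month assumption follows: "We conservatively anticipated 30% 7-day ppa at 12-months in the CS-CBT condition, and 14% in the control condition". The section ends with a final N of 150 participants completing all assessments.

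Under Intervention conditions, the control regimen (standard group CBT with nicotine patch) is described with results from the same earlier trial, which "found 7-day ppa rates of 70% at the EOC, 52% at the 3-month follow-up, and 46% at the 6-month follow-up post counseling".

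Three other statements bear on the reading. The Abstract plans to randomize at least 247. Statistical analyses defines the intention-to-treat (ITT) approach as counting missing participants as smokers. The Discussion reports about 70% retention in the same earlier trial.

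**The concern.** The two sections give different values for one quantity: same earlier trial, regimen, outcome and time point. The later points differ as well. The intervention section's 3-month rate (52%) is already higher than the sample-size section's EOC rate (51%).

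The figure matters because it sets the planned effect. Against 75%, a control rate of 51% leaves 24 points and a control rate of 70% leaves 5. The trial tests whether cultural adaptation adds anything to an active, effective control, so the assumed control rate largely decides whether a null result at EOC would be informative. Without denominators the reader cannot tell whether 75% and 51% may be compared at all. One could be a rate among those assessed and the other a rate among all enrolled.

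**Working it through.** **Inputs.** Control EOC 51% (Sample size and power) or 70% (Intervention conditions). CS-CBT EOC 75%, m = 4 assessments, within-subject correlation 0.60, two-sided 5%, 65 per arm (all Sample size and power). 75 per arm is half of the final N of 150. About 123 per arm is half of 247.

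**Formula.** Single time point, with p̄ the mean of the two rates and d their difference:

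n per arm = [1.96·√(2p̄(1−p̄)) + 0.842·√(p₁(1−p₁) + p₂(1−p₂))]² / d²

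For repeated measures, n is multiplied by (1 + (m−1)ρ)/m = (1 + 3 × 0.60)/4 = 0.70. The protocol cites a textbook page for its formula, which is not at hand, so this factor is an assumption. Clustering by therapy group is ignored throughout.

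**The plan's own figure.** 51% v 75%: p̄ = 0.63, d = 0.24, n = (1.338 + 0.557)²/0.0576 = 62.3, so 63 per arm. Power at 65 per arm is 82%. The stated 65 is therefore close to a plain EOC comparison. With the 0.70 factor, n = 44 and power at 65 is 93%, so the assumed factor does not return 65 from these rates. How the protocol reached 65 is not established.

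**With 70% as control.** p̄ = 0.725, d = 0.05, n = (1.238 + 0.531)²/0.0025 ≈ 1,251 per arm, or 876 with the 0.70 factor.

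| EOC contrast | Per arm | Power, single time point | Power, m = 4, ρ = 0.60 |
|---|---|---|---|
| 51% v 75% | 65 | 82% | 93% |
| 70% v 75% | 65 | 9% | 12% |
| 70% v 75% | 75 | 10% | 13% |
| 70% v 75% | 123 | 14% | 18% |

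**Three months.** The sample-size section implies a control rate of 51% × 0.80 = 40.8% if the 20% relapse is relative, or 51 − 20 = 31% if absolute. The intervention section gives 52%, which is 11 to 21 points higher.

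**Could the two figures be one result on two denominators?** 70% abstinent among those retained, times 70% retention, is 0.70 × 0.70 = 49% with missing counted as smoking. That is near 51%, so the explanation is plausible.

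**What that would imply for the 75%.** If 75% is already a missing-as-smoker rate, the 24 points stand. If it is a completer rate, scaling it by the same ratio (51/70, for illustration only) gives 75% × 51/70 = 54.6%. The difference from 51% is then about 4 points, with power of 6% to 7% at 65 per arm and 8% to 10% at 123.

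**The 12-month assumption.** 14% v 30% needs 104 per arm as a single time point, or 73 with the 0.70 factor.

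| Per arm | Power, single time point | Power, m = 4, ρ = 0.60 |
|---|---|---|
| 65 | 60% | 75% |
| 75 | 66% | 81% |
| 123 | 86% | 95% |

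**The case against.** The strongest reply is that nothing shows 70% to be the right planning rate. The retention arithmetic makes it plausible that 70% is a completer rate and 51% its missing-as-smoker counterpart, in which case 51% is the one that matches the ITT analysis. This stands, and it rules out saying that the trial is underpowered. It does not settle the matter: the protocol never states this explanation, the basis of the 75% stays unknown, and the final N is expressed in completers, which fits poorly beside a missing-as-smoker rate.

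The second reply is that the design does not hang on the EOC contrast alone. This also stands. The 12-month rates are a separate assumption and give about 80% power at 75 per arm under the assumed repeated-measures formula. A reader might infer that the whole planned effect depends on the choice between 51% and 70%; the document does not support that.

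Third, the repeated-measures factor is assumed and gives 44 rather than 65 for the plan's own rates, so the exact figures for the 70% case are conditional. The single-time-point results, which come within two participants of the stated 65, show the same fall.

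A reader might also hold against the plan that 14% at 12 months is called conservative when the intervention section has 46% at 6 months. That would mean (46 − 14)/46, about 70%, of abstainers relapsing in six months. But the two rates may have different denominators, no 12-month rate from the earlier trial is given, and the planned gap does narrow from 24 to 16 points. The choice of word is an editorial matter.

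**Conclusion.** The concern holds as an unreconciled contradiction in an input to the sample size. The protocol attributes both 51% and 70% to the same regimen, outcome, time point and earlier trial, and gives no denominator for either or for the 75% set against them. The stated 80% power at EOC is therefore verifiable only on the unstated condition that 75% and 51% share a basis.

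If 70% is the comparable rate, EOC power at 65 per arm falls from 82% to 9% (single time point) or from 93% to 12% (assumed repeated-measures formula). Randomizing 247 raises it only to 14% to 18%. Which case applies cannot be determined from the document. The loss is confined to the EOC and early follow-up contrasts; the separate 12-month assumption is not directly affected.

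**What to change.** In Sample size and power and in Intervention conditions:

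- Reconcile the 51% and the 70%, and state for each rate, including the 75% pilot rate, the number abstinent, the denominator and how missing participants were counted.
- Put both arms' planning rates on the ITT definition: all enrolled, missing counted as smoker.
- Say whether the 20% relapse and the 23% reduction are relative or absolute, and to which arm the 23% applies.
- Rerun the stated formula with those rates, and report the power or the smallest detectable difference at the planned enrolment of at least 247.
- Give the basis for the 12-month rates of 30% and 14%.

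The cost is one recalculation and a few sentences. The stated power may come out less favourable. No extra participants are needed.
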